### Statistical methods

#### Sample size calculation

Sample size calculation will be based on the co-primary outcomes of the RCT. A sample of 78 patients per group will provide 80% power to detect the difference in both peak VO_2_ = 1.5 (mL/kg/min) and MLHFQ total score = 10 points between groups at a two-tailed significance level of 5%. This accounts for the standard deviation of peak VO_2_ = 3 mL/kg/min and MLHFQ score = 20 points and meets clinically important difference (peak VO_2_ = 1 mL/kg/min [46] and MLHFQ score = 5 points [33]). This would require 156 participants, inflated to 200 to account for the loss to follow-up of approximately 20% of participants. Because each primary endpoint can characterize a clinically meaningful benefit of the intervention on its own, we will use the “or decision rule,” meaning that the study will be regarded as successful if one of the two primary endpoints improves significantly in the intervention group.

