### Quantitative data analysis

Statistical analysis will be performed in a blinded manner by qualified statisticians using PASW Statistics 18.0 (IBM SPSS Inc., Armonk, New York, USA), SAS 9.2 (SAS Institute Inc., Cary, USA), and Stata (Version 13.0, StataCorp). The level of significance will be set at *p* < 0.05. Baseline variables will be reported by groups, descriptively. For the outcome variables, continuous data will be summarized as mean and standard deviation or range, or as median and interquartile range, and categorical data as counts and percentages. The primary analyses for primary and secondary outcome variables will be based on the intention-to-treat population approach, using data collected at baseline and at the 12th week. Differences in terms of outcomes between groups will be compared using an independent *t* test/Mann-Whitney *U* test, as appropriate. For the two co-primary outcomes, the significance level will be Bonferroni-corrected (*α* = 0.05/2 = 0.025). The effect of intervention on outcomes will also be analyzed using multivariate statistical models, with adjustments for baseline score of the outcome variable (where applicable), as well as gender, age, co-morbidities and other variables that are of clinical importance. In addition, multiple imputation methods will be used as a sensitivity analysis to address the issue of missing data. Subgroup analysis will be performed according to gender, cardiac functional classification, left ventricular ejection fraction classifications, and other variables of clinical importance. The secondary analyses for outcome variables will be undertaken as repeated measure analysis and mixed-effects models using all assessment points (4, 8 and 12 weeks). Sensitivity analysis will be performed, including, but not limited to, the analysis for outcome variables using a per-protocol population. Safety will be evaluated by tabulations of AEs, and will be presented with descriptive statistics for each group. A chi-square test or a Fisher’s exact test will be used to compare the frequency difference in AEs between the two groups. To explore potential factors which might influence adherence, a logistic regression model and a linear mixed-effects model will be used and adjusted for potential confounders. Adherence-related data will be taken from exercise log records.

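### The sample size sentence claims 80% power for both co-primary differences at a two-sided 5% level; 78 per group gives 80% for each endpoint separately at the 2.5% Bonferroni level

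*Protocol article*

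**What the plan says.** Under *Sample size calculation* the protocol article claims: "A sample of 78 patients per group will provide 80% power to detect the difference in both peak VO_2" and MLHFQ. The planned differences are given as "1.5 (mL/kg/min) and MLHFQ total score = 10 points between groups", and the standard deviations as "3 mL/kg/min and MLHFQ score = 20 points" (each pair listed with peak VO2 first). The level is stated as "between groups at a two-tailed significance level of 5" per cent. The resulting 156 patients are raised to 200 for a loss of about 20%.

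The same paragraph adopts an either-endpoint rule: "the study will be regarded as successful if one of the two primary endpoints improves significantly in the intervention group".

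Under *Quantitative data analysis* the test is fixed: "Differences in terms of outcomes between groups will be compared using an independent *t* test/Mann-Whitney *U* test, as appropriate". The level for the two primary outcomes is then set: "For the two co-primary outcomes, the significance level will be Bonferroni-corrected", with the value written out as 0.05/2 = 0.025.

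**The concern.** The sample size paragraph gives 5% as the level and does not say that it is an overall level to be divided between two endpoints. The analysis section tests each endpoint at 2.5%. Someone who recomputes the sample size from the paragraph's own inputs, one endpoint at a time, gets a number other than 78.

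The word *both* adds a second difficulty. Three powers can be quoted for a trial with two primary endpoints: for each endpoint singly, for both together, and for at least one. They differ materially here. The sentence reads most directly as the power for both together, while the success rule two sentences later needs one endpoint. An ethics committee, a monitoring committee or a later reader could take from it a four-in-five chance of showing both effects if both are real. That would be an overstatement for the planned test.

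**Working it through.** **Inputs from the protocol.** Differences of 1.5 mL/kg/min and 10 points; SDs of 3 mL/kg/min and 20 points; 78 per group; 1:1 allocation; 80% power; independent t test; 5% in the sample size section and 2.5% per endpoint in the analysis section. The correlation between the two endpoints is not given; I assume 0 to 0.8 and show the range.

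**Step 1: standardised effects.** 1.5/3 = 0.5 and 10/20 = 0.5. The endpoints are equivalent for planning, so one calculation serves for each.

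**Step 2: reproduce the 78.** The normal approximation is n per group = 2(z₁₋α/₂ + z₀.₈)²/d², with d = 0.5, so 2/d² = 8.

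- Two-sided 5%: 8 × (1.960 + 0.842)² = 62.8, so 63.
- Two-sided 2.5%: 8 × (2.241 + 0.842)² = 76.0, so 77.

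The exact t test uses the noncentral t distribution with 2n − 2 degrees of freedom and noncentrality d√(n/2). At n = 78 this is 0.5 × √39 = 3.12 on 154 degrees of freedom.

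| Two-sided level per endpoint | Smallest n per group for 80% | Power at 78 per group |
|---|---|---|
| 5% | 64 | 87.3% |
| 2.5% | 78 | 80.4% |

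At 2.5%, 77 per group gives 79.8%, so 78 is the exact t-test answer at that level. The plan's figure is reproduced for each endpoint singly at the Bonferroni level, and not for each endpoint at an unsplit 5%.

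**Step 3: power for both and for at least one, at 2.5% each, 78 per group.** With independent endpoints, power for both = 0.804² = 0.646, and power for at least one = 1 − (1 − 0.804)² = 0.962. In general, power for at least one = 2 × (power for each) − (power for both). With correlation, simulation of the two t tests (40,000 trials per setting) gives:

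| Assumed correlation | Each | Both | At least one |
|---|---|---|---|
| 0 | 80% | 64.6% | 96.2% |
| 0.3 | 80% | 67.4% | 93.5% |
| 0.5 | 80% | 69.1% | 91.7% |
| 0.8 | 80% | 73.4% | 87.5% |

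Power for both stays below 80% throughout this range, and power under the trial's own success rule stays above it.

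**Step 4: the most literal reading, both endpoints, each at 5%.** The same simulation gives joint power of 76.1%, 77.7%, 79.2% and 82.2% at correlations 0, 0.3, 0.5 and 0.8. This comes close to 80% at moderate correlation.

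**Step 5: dropout.** 156/(1 − 0.20) = 195, so 200 is sufficient.

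**The case against.** The strongest defence is that nothing in the design is wrong. Read 5% as the overall level, divided as the analysis section divides it, and read *both* as *each of the two*. Then 78 per group, 80% per endpoint, 2.5% each, an overall 5% and success on either endpoint form one standard, coherent design, and the exact agreement at 78 makes it likely that the size was calculated that way. The same paragraph says that each endpoint can carry a benefit by itself, which supports this reading. All of this stands. A reader might infer that the level, the power and the success rule come from different designs; the documents do not support that. What remains is that the sample size sentence does not state the division and does not say *each*.

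It can also be said that 78 fits the literal sentence, since joint power with each endpoint at 5% is about 76–82%. So it would be too strong to say that no other reading comes near 80%. But that reading needs a correlation the protocol never states, an all-endpoints requirement that conflicts with the either-endpoint rule, and a level that conflicts with 2.5%. It does not rescue the wording.

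A further tempting reading is that the success rule, with its reference to improvement within the intervention group, allows success on a within-arm change that the control arm might share. The documents rule this out: the sample size section powers a difference between groups, the analysis section compares groups by an independent-samples test, and the primary hypothesis in the Background is stated against usual medications alone. No within-arm test is planned.

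**Conclusion.** The point holds as a misstatement of level and power in the sample size section, not as an error in the sample size. For each endpoint at the planned two-sided 2.5%, 78 per group gives 80.4% power. The stated 5%, applied per endpoint without division, would correspond to 64 per group, or to 87.3% power at 78. If both planned effects are real, the trial shows both with a probability of about 65–73% and meets its own success rule with a probability of about 87–96%.

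The per-endpoint figures rest on the protocol's differences and SDs and on a t test. The joint figures also rest on an assumed correlation of 0 to 0.8. The trial is not underpowered for its declared rule, the planned Bonferroni split keeps the overall error for the two primary tests at 5%, and recruitment need not change.

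**What to change.** Keep 156 evaluable and 200 randomised patients. Replace the power sentence with, for example: *78 evaluable patients per group give 80% power for each primary endpoint separately at a two-sided 2.5% level (overall 5%, Bonferroni), assuming differences of 1.5 mL/kg/min (SD 3) in peak VO2 and 10 points (SD 20) in MLHFQ total score.* Remove the suggestion of 80% power to show both. Joint or either-endpoint power need not be quoted; if it is, mark it as depending on an assumed correlation.

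As a minor wording point, state the success rule as a between-group difference in favour of the intervention on at least one primary endpoint at two-sided 2.5%, which is what the analysis section already plans.

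The cost is a change of wording in two sentences. No patients are added, and no test or significance level changes. If a figure for showing both endpoints is reported, it will be lower than readers may have assumed.

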### Quantitative data analysis

Statistical analysis will be performed in a blinded manner by qualified statisticians using PASW Statistics 18.0 (IBM SPSS Inc., Armonk, New York, USA), SAS 9.2 (SAS Institute Inc., Cary, USA), and Stata (Version 13.0, StataCorp). The level of significance will be set at *p* < 0.05. Baseline variables will be reported by groups, descriptively. For the outcome variables, continuous data will be summarized as mean and standard deviation or range, or as median and interquartile range, and categorical data as counts and percentages. The primary analyses for primary and secondary outcome variables will be based on the intention-to-treat population approach, using data collected at baseline and at the 12th week. Differences in terms of outcomes between groups will be compared using an independent *t* test/Mann-Whitney *U* test, as appropriate. For the two co-primary outcomes, the significance level will be Bonferroni-corrected (*α* = 0.05/2 = 0.025). The effect of intervention on outcomes will also be analyzed using multivariate statistical models, with adjustments for baseline score of the outcome variable (where applicable), as well as gender, age, co-morbidities and other variables that are of clinical importance. In addition, multiple imputation methods will be used as a sensitivity analysis to address the issue of missing data. Subgroup analysis will be performed according to gender, cardiac functional classification, left ventricular ejection fraction classifications, and other variables of clinical importance. The secondary analyses for outcome variables will be undertaken as repeated measure analysis and mixed-effects models using all assessment points (4, 8 and 12 weeks). Sensitivity analysis will be performed, including, but not limited to, the analysis for outcome variables using a per-protocol population. Safety will be evaluated by tabulations of AEs, and will be presented with descriptive statistics for each group. A chi-square test or a Fisher’s exact test will be used to compare the frequency difference in AEs between the two groups. To explore potential factors which might influence adherence, a logistic regression model and a linear mixed-effects model will be used and adjusted for potential confounders. Adherence-related data will be taken from exercise log records.

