### Outcomes measures

#### Primary outcomes

Two co-primary outcomes are the change in exercise capacity measured as peak VO_2_ (mL/kg/min) from CPX and disease-specific quality of life measured as the MLHFQ total scores between baseline and 12 weeks. Co-primary endpoints are chosen so that a comprehensive picture of the treatment effect can be obtained [30]. The objectives of cardiac rehabilitation are to positively influence disease progression and prognosis; and to improve patients’ overall quality of life [28]. Exercise capacity and quality of life are two different domains of interest in rehabilitation research [30]. Peak VO_2_ is the “gold standard” for assessing exercise capacity, and is an important predictor of prognosis in CHF patients [31]. MLHFQ is a validated and commonly employed disease-specific quality of life instrument in CHF which covers physical, psychological, and socioeconomic dimensions [32].

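### The deciding test of both co-primary endpoints leaves out baseline as a covariate, so power and precision available from data already collected are forgone

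*Protocol article*

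**What the plan says.** The Primary outcomes section defines both endpoints as changes over 12 weeks: "Two co-primary outcomes are the change in exercise capacity measured as peak VO_2_ (mL/kg/min) from CPX", together with the MLHFQ total score over the same interval. Peak VO2 is measured at baseline and week 12, and the MLHFQ at baseline and weeks 4, 8 and 12.

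Under Quantitative data analysis, the primary analyses follow intention to treat, "using data collected at baseline and at the 12th week". The between-group test is then named: "Differences in terms of outcomes between groups will be compared using an independent *t* test/Mann-Whitney *U* test, as appropriate". A Bonferroni level of 0.025 applies to each co-primary endpoint. Adjusted models come next, as an addition: "The effect of intervention on outcomes will also be analyzed using multivariate statistical models". Their covariates are the outcome's baseline score where there is one, several patient characteristics, and an open-ended set of clinically important variables. Mixed-effects models using all visits are labelled secondary; multiple imputation and the per-protocol analysis are sensitivity analyses.

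The Sample size calculation gives 78 per group for 80% power, differences of 1.5 mL/kg/min and 10 points, and SDs of 3 and 20. It does not say whether these are SDs of change or of the 12-week score, and it gives no baseline to 12-week correlation.

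**The concern.** A t test on change uses baseline by subtraction, which fixes the coefficient on baseline at 1. ANCOVA estimates that coefficient. In a randomised comparison with equal variances at the two visits, ANCOVA has the smaller residual variance whenever the correlation is below 1, and it corrects for chance baseline imbalance. The plan already contains a baseline-adjusted model but gives it the supporting role, while the less efficient test decides the trial.

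What is at stake is power and confidence interval width on both co-primary endpoints, at no saving in data. A lesser matter is that the deciding test is left as one of two. The t test compares means, which is the scale of the planned 1.5 mL/kg/min and 10 points; the Mann-Whitney test compares ranks and does not estimate a mean difference.

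**Working it through.** **Inputs from the plan.** Differences 1.5 and 10; SDs 3 and 20; so the standardised difference is 1.5/3 = 10/20 = 0.5 for both endpoints. 78 per group, 1:1 allocation, two-sided level 0.05/2 = 0.025 per endpoint.

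**Assumptions.** The correlation r between baseline and week 12 is not given, so a range is shown. Variances at the two visits are taken as equal.

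**Step 1: the plan's own figure.** For an unadjusted two-sample t test with standardised difference 0.5 and level 0.025, 80% power needs 77.3, that is 78 per group; power at 78 is 0.804. The stated figure reproduces. At 0.05 the same calculation needs 64 per group and gives 0.873 at 78. The calculation was therefore made at the Bonferroni level for an unadjusted test, although the Sample size calculation names only the overall 5%.

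**Step 2: if 3 and 20 are SDs of change.** Residual variance of ANCOVA relative to change is (1 + r)/2, so the standardised difference becomes 0.5/√((1 + r)/2).

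| r | (1 + r)/2 | Standardised difference | ANCOVA power | t test on change | Equivalent extra patients, 1/ratio − 1 |
|---|---|---|---|---|---|
| 0.5 | 0.75 | 0.577 | 0.909 | 0.804 | 33% |
| 0.7 | 0.85 | 0.542 | 0.868 | 0.804 | 18% |
| 0.9 | 0.95 | 0.513 | 0.825 | 0.804 | 5% |

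Confidence intervals shrink by the square root of the ratio: √0.75 = 0.87, √0.85 = 0.92, √0.95 = 0.97.

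**Step 3: if 3 and 20 are SDs of the 12-week score.** Relative to the score variance, change has variance 2(1 − r) and ANCOVA has residual variance 1 − r². The right comparator is still the t test on change, because change is the defined endpoint.

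| r | 2(1 − r) | Power, t test on change | 1 − r² | Power, ANCOVA |
|---|---|---|---|---|
| 0.3 | 1.40 | 0.647 | 0.91 | 0.843 |
| 0.5 | 1.00 | 0.804 | 0.75 | 0.909 |
| 0.7 | 0.60 | 0.961 | 0.51 | 0.982 |

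**Step 4: the open choice of test.** If the data are normal and the Mann-Whitney test is used, its relative efficiency of 0.955 gives an effective 78 × 0.955 = 74.5 per group and power of about 0.78. In 20,000 simulated null trials with 78 per group at 0.025, choosing by a Shapiro normality pre-test rejected in 0.026 (normal data) and 0.025 (lognormal data). Taking the smaller of the two p-values rejected in 0.030 and 0.038.

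**The case against.** The strongest reply is that nothing is broken. A change-score comparison is valid under 1:1 randomisation, the sample size was computed for that kind of test and reproduces, and a trial may choose a simple primary analysis. The size of the gain rests on a correlation the document does not give; with high correlation and SDs of change, it is only from 80% to 83%. All of this stands, and it limits the point to efficiency.

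Three stronger readings are tempting, and the document does not support them.

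- A reader might quote a gain from 80% to 98% at r = 0.7. That compares ANCOVA with a t test on 12-week scores, but the Primary outcomes section defines the endpoint as change. Against a t test on change, the gain in that case is from 96% to 98%.
- A reader might infer that no rule says which p-value decides. The analysis section does rank its analyses: the t test or Mann-Whitney comparison is primary, adjusted models are additional, and mixed models are secondary. Only the choice between the two simple tests is open.
- A reader might infer an inflated type I error. The wording covers primary and secondary outcomes together, statisticians are to be blinded to allocation, and a criterion may sit in an analysis plan that is not shown. A normality pre-test keeps the error near 0.025. The inflation to 0.030–0.038 needs the smaller p-value to be picked, which the protocol does not propose.

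The reply does not defend the ranking itself. The article states which analysis is primary, so this is not detail left to another document, and no other section makes the adjusted model primary.

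**Conclusion.** The point holds as a matter of efficiency. The primary test is valid and delivers its planned 80% if the SDs are those of the endpoint tested, but it leaves unused power that the baseline measurements would supply. The gain is about 3 to 11 percentage points if the SDs are of change (r from 0.9 down to 0.5). If they are of the 12-week score, it is about 2 to 20 points (r from 0.7 down to 0.3).

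It would be wrong to call the trial underpowered as planned. Power on change falls below 80% only if the SDs are score SDs and r is below 0.5, and the document settles neither. The sizes rest on assumed correlations and equal variances; the direction, in favour of ANCOVA, does not depend on which value of r below 1 is assumed. The unstated choice between t test and Mann-Whitney is a minor matter that would not justify a point on its own.

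**What to change.** Make the primary test of each co-primary endpoint, at two-sided 0.025, a linear model of the 12-week value on randomised group and that endpoint's own baseline value, with no discretionary covariates. Report the adjusted mean difference with its confidence interval. Using change as the dependent variable with the same baseline covariate gives the identical treatment estimate, so the endpoint definition need not change.

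Keep the t test or Mann-Whitney test as a sensitivity analysis, which also removes the open choice from the deciding test. Keep the model with gender, age, co-morbidities and other covariates as a supporting analysis. State in the Sample size calculation whether 3 and 20 are SDs of change or of the 12-week score.

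The cost is wording only: no new data, visits or patients. The model assumes a roughly linear relation with baseline, a mild assumption at about 80 to 100 per group. The change should be made before any unblinded outcome data are seen.

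### Holm's procedure would be a one-sentence improvement on the valid plain Bonferroni test: same 5% family-wise control, more power to confirm the second primary endpoint

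*Protocol article*

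**What the plan says.** Three parts of the protocol article bear on this.

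- **Quantitative data analysis** fixes the correction: "For the two co-primary outcomes, the significance level will be Bonferroni-corrected", with the level given as 0.05/2 = 0.025. It describes no step-down or other sequential rule.
- **Sample size calculation** sets an either-endpoint rule: "the study will be regarded as successful if one of the two primary endpoints improves significantly in the intervention group". It also gives the planning figures: "A sample of 78 patients per group will provide 80% power to detect the difference in both peak VO_2_ = 1.5 (mL/kg/min"), an "MLHFQ total score = 10 points between groups", and "This accounts for the standard deviation of peak VO_2_ = 3 mL/kg/min and MLHFQ score = 20 points". The level is worded as "between groups at a two-tailed significance level of 5" per cent.
- **Primary outcomes** explains why there are two endpoints: "Co-primary endpoints are chosen so that a comprehensive picture of the treatment effect can be obtained".

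**The concern.** Under plain Bonferroni each endpoint is held to 0.025 even after the other has been rejected. At that point half of the 5% error allowance is no longer needed for the hypothesis already rejected, and Holm passes it to the one that remains.

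Suppose peak VO2 gives p = 0.01 and MLHFQ gives p = 0.04. Under the plan only peak VO2 is confirmed. Under Holm both are, at the same family-wise error rate. The trial is a success either way. What is at stake is whether the second domain can also be claimed as a confirmed effect, which is useful in a trial that chose two endpoints to cover two domains.

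**Working it through.** **Inputs.** From Sample size calculation: 78 per group; differences 1.5 mL/kg/min and 10 points; SDs 3 and 20. The standardised effects are 1.5/3 = 0.5 and 10/20 = 0.5. Allocation is 1:1. The article gives no correlation between the endpoints, so 0 to 0.7 is assumed.

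**Reproducing the plan's figure.** By normal approximation, n per group = 2(z₁₋α/₂ + z₀.₈)²/d².

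- At two-sided 0.025: 8 × (2.241 + 0.842)² = 76.04, so 77. The exact t calculation gives 78, with 80.4% power at n = 78.
- At two-sided 0.05: 8 × (1.960 + 0.842)² = 62.8, so 63 (64 by t).

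The 78 is therefore the Bonferroni-level figure, although that section's wording says 5%. The 80% holds for each endpoint separately, not for both jointly.

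**Power at independence, in closed form.** The mean of each z statistic is 0.5 × √(78/2) = 3.122. Power for one endpoint is b = Φ(3.122 − 2.241) = 0.811 at 0.025 and h = Φ(3.122 − 1.960) = 0.877 at 0.05.

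- At least one significant, either method: 1 − (1 − b)² = 0.964.
- Both, Bonferroni: b² = 0.658.
- Both, Holm (both p ≤ 0.05 and at least one ≤ 0.025): h² − (h − b)² = 0.766.
- One given endpoint, Holm: b + (h − b)b = 0.865, against 0.811.

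**Power with correlation.** Simulation of bivariate normal z statistics, 2 million draws per row, effect 0.5 on both endpoints:

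| Correlation | At least one (either method) | Per endpoint, Bonferroni | Per endpoint, Holm | Both, Bonferroni | Both, Holm |
|---|---|---|---|---|---|
| 0 | 96.5% | 81.1% | 86.5% | 65.9% | 76.6% |
| 0.3 | 94.0% | 81.1% | 85.9% | 68.2% | 77.9% |
| 0.5 | 92.0% | 81.1% | 85.6% | 70.2% | 79.1% |
| 0.7 | 89.5% | 81.1% | 85.0% | 72.7% | 80.6% |

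The gain in confirming both is about 8 to 11 points, and per endpoint about 4 to 5 points.

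**Error rate.** With no effect on either endpoint, the chance of any rejection is 4.9 / 4.8 / 4.7 / 4.3% across the four correlations, the same for both methods.

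**Only one endpoint truly affected.** Power for that endpoint is 81.1% with Bonferroni and 81.2–81.3% with Holm, so almost nothing is gained. The rejection rate for the unaffected endpoint rises from 2.5% to 4.0–4.5%, still within 5%.

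**One smaller effect, at independence.** Suppose peak VO2 has d = 0.5 and MLHFQ changes by the 5-point clinically important difference that the section cites (d = 5/20 = 0.25). Power for MLHFQ is 0.248 at 0.025 and 0.345 at 0.05. Holm gives 0.248 + (0.345 − 0.248) × 0.811 = 0.327, a rise from about 25% to 33%.

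**The case against.** The strongest reply is that nothing here is wrong. Bonferroni at 0.025 holds the family-wise error at or below 5% under any correlation, matches the either-endpoint rule, and is the level at which 78 per group is reproduced. The cost of the correction has thus already been paid in the sample size. Both methods need the smaller p-value to reach 0.025, so the probability of success is identical. All of this stands, and it makes the point an improvement rather than a correction.

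The reply also holds that the stated reason for two endpoints explains why two domains are measured and does not commit the trial to rejecting both hypotheses. That is fair: the either-endpoint rule governs success. It limits the weight of the point but does not remove the gain.

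The third part concerns intervals. Bonferroni's 97.5% intervals always agree with its tests. If they are kept alongside Holm, they conflict with the Holm decision in every case where Holm adds a rejection, since the second p-value then lies between 0.025 and 0.05. This is a real, small downside, and preferring matching intervals is a legitimate choice.

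A reader might infer that type I error is uncontrolled, that the trial is underpowered for its own criterion, or that a second endpoint with p between 0.025 and 0.05 would be presented as a negative result. The article supports none of these. The error rate is held, the success criterion has about 90–96% power under the planning assumptions, and nothing says how such a second result would be labelled.

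**Conclusion.** The plan is valid as written, and Holm is a cheap improvement on it. That Holm controls the same error rate and rejects everything Bonferroni rejects does not depend on any assumption. The size of the gain does: it rests on 78 evaluable patients per group, a true standardised effect of 0.5 on both endpoints, the normal approximation, and a correlation of 0 to 0.7 that the article does not give. Under those conditions power to confirm both endpoints goes from about 66–73% to 77–81%. The chance of success and the required sample size stay as they are, and the benefit nearly vanishes if only one endpoint responds.

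**What to change.** In Quantitative data analysis, replace the Bonferroni sentence with:

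> The two primary endpoints will be tested with the Holm procedure at a family-wise two-sided 5%: the smaller p-value against 0.025 and, if significant, the larger against 0.05.

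Add that 97.5% confidence intervals will be reported for each endpoint as conservative simultaneous intervals, and that decisions rest on the Holm-adjusted p-values. The interval for the second endpoint will include zero whenever that endpoint is rejected with p between 0.025 and 0.05, and saying so beforehand avoids an apparent contradiction in the report.

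The cost is two sentences and that mismatch. The either-endpoint rule, the 78 per group and the recruitment target of 200 do not change, and no new data are needed. The change must be made before unblinded results are available.
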